These preliminary results suggest that a single-session BI-VT is suitable for the perinatal context. Building on this pilot study, a randomised controlled trial (RCT) will then allow to control for other potential confounding factors, such as the time between the trauma and the intervention.^31^ Since, to our knowledge, no equivalent single-session intervention aimed at reducing CB-IM exists, a comparative treatment control group was not applicable. Therefore, to test the efficacy of a BI-VT to reduce CB-PTSS and to allow all help-seeking participants to benefit from the likely positive effects of this BI-VT, this RCT will include a waitlist control group (WCG) as a comparator. As waitlists can create a nocebo condition, which might bias participants’ self-reported symptoms^32^ and artificially increase the estimated effects of the experimental intervention,^33^ participants will be blind to group allocation in an effort to limit these biases. Even though this RCT including a WCG will not allow to study the specific effect of the mechanisms of this BI-VT on CB-PTSS in comparison to other interventions, it will bring more evidence to define this BI-VT as potentially *efficacious* to reduce CB-PTSS.^31^ Given the lack of evidence supporting current interventions to treat established CB-PTSS,^34^ developing a single-session, low cost, easily accessible and evidence-based intervention would be of great clinical value and might reduce long-term difficulties of mothers after traumatic childbirth.

One challenge for the translational research on memory reconsolidation is to identify if each supposed memory process is taking place and at which point.^35^ No markers of these memory processes exist so far, but emotional arousal may be used to infer if participants have been sufficiently engaged in the narration of their traumatic memory to trigger memory reactivation. Previous findings revealed that a decrease in emotional arousal after playing Tetris is associated to an increased responsiveness to a similar BI-VT.^25^ Therefore, we will include emotional and physiological measures of arousal (eg, subjective distress and heart rate variability (HRV)^36 37^) to explore conditions enabling a successful implementation of a BI-VT in the perinatal context. In the future, such an assessment of physiological/emotional arousal could guide a personalised adaptation of this type of intervention.^38^

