### Secondary outcomes

Secondary outcomes will be:

The change in CB-PTSS between: (a) baseline and at 2 weeks postimmediate intervention across groups, (b) baseline and follow-up in the IIG.The change in the number of CB-IM between baseline and follow-up in the IIG.The acceptability of the intervention in both groups.

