### Sample size calculation

A sample size calculation was conducted for our primary and secondary outcomes based on the results obtained from the pilot study,^27^ assessing the efficacy of the same intervention using a single-group pre–post design, and from laboratory studies using RCT designs to assess the efficacy of a similar BI-VT.^23 24^ A sample size of 90 participants (45 allocated in each group) is estimated to be necessary to detect the effect of the intervention on our primary and secondary outcomes with an 80% power (α = 0.05). Based on our experience with this study population,^11 27^ a conservative estimate of a 30% drop-out and exclusion was assumed. We therefore plan to recruit 120 participants in total.

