### Data management and statistical analysis

Participants’ entries in electronic diaries and questionnaires will be directly stored in the REDCap software. The research staff will enter manually the rest of the data collected during the screening, the intervention and paper diaries in REDCap. All data will be hosted on a high security server of the Lausanne University Hospital performing automatic continuous backups. All primary outcome data and a random 5% of the rest of the data will be double-checked. Independent and blind coders will inspect diary entries to detect any non-compliance with instructions and count the number of CB-IM. A blind statistician will perform the analyses. To ensure blinding of the coders and the statisticians, they will receive a dataset not indicating which allocation group corresponds to the IIG or WCG. Only the study team will have access to the full coded trial dataset.

For primary outcomes, group differences regarding change of the number of CB-IM between baseline and the 2 weeks postimmediate intervention will be analysed using repeated-measures analyses (intention-to-treat analyses). For the secondary outcomes, repeated-measures analyses will be performed to analyse group differences concerning CB-PTSS between baseline and at 2 weeks postimmediate intervention. Logistic regression analyses will also compare the proportion of participants meeting the diagnostic criteria for CB-PTSD across time and groups. Furthermore, repeated measures analyses will serve to analyse change in the number of CB-IM and CB-PTSS between baseline and follow-up in the IIG. Group differences regarding the proportion of participants meeting the diagnostic criteria for CB-PTSD will be analysed with logistic regression analyses. The mean score of the intervention acceptability will be calculated across both groups. Additional post-hoc analyses conducted will be described as such in publications. Missing data will be dealt with using multiple imputation procedures, if appropriate.

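### Two secondary outcomes are one-arm changes without a comparator, yet the sample-size statement counts them among the outcomes on which the intervention's effect will be detected

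*Protocol article*

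**What the plan says.** Under Secondary outcomes, the article lists two changes measured in the Immediate Intervention Group (IIG) alone. One is the change in childbirth-related post-traumatic stress symptoms (CB-PTSS) between "b) baseline and follow-up in the IIG". The other is "The change in the number of CB-IM between baseline and follow-up in the IIG", where CB-IM are childbirth-related intrusive memories. Data management and statistical analysis gives the method: "repeated measures analyses will serve to analyse change in the number of CB-IM and CB-PTSS between baseline and follow-up in the IIG".

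T4 (delayed intervention) has the WCG treated on day 30. T6 (follow-up) has the IIG alone assessed in weeks 5 and 6 after its session, and the WCG excused to balance burden. Table 1 agrees.

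Sample size calculation then says: "A sample size of 90 participants (45 allocated in each group) is estimated to be necessary" and continues "to detect the effect of the intervention on our primary and secondary outcomes with an 80% power (α = 0.05". It does not set the two one-arm outcomes apart.

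The Introduction, in the part on developing the intervention for the perinatal context, says that after the uncontrolled pilot a randomised trial will make it possible to "control for other potential confounding factors, such as the time between the trauma and the intervention".

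**The concern.** An effect of the intervention is a contrast with what would have happened without it. For these two outcomes the plan observes only the treated arm before and after, so the contrast is not estimated, whatever the sample size. The observed change combines any effect of the session with natural recovery as time since the birth passes, with any effect of keeping a diary, and with regression to the mean.

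Selection makes regression to the mean a real possibility. Under Population, recruitment, group allocation and blinding, entry requires at least four CB-IM in the 2 weeks before screening. Women with fewer than two at baseline are then dropped from the relevant analyses. The second rule truncates from below the very value from which change is measured, which favours an apparent fall.

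At stake is what the trial may conclude at 6 weeks. A significant fall in the IIG, reported beside a statement that the trial was powered to detect the intervention's effect on this outcome, could be read as evidence of lasting benefit. In design it would be no stronger than the single-group pilot. The list of strengths and limitations notes that the waitlist is not an active comparator, but not that the 6-week results have no comparator.

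**Working it through.** **Is there any comparator at follow-up?** Baseline is days 1 to 14 and the IIG session is day 15. Weeks 5 and 6 after it are about days 44 to 57. The WCG is treated on day 30, before that window opens, so it could not serve as an untreated control there even if it were assessed. The midpoints of the baseline and follow-up diaries are about days 7.5 and 50.5, which is 43 days or roughly 6 weeks apart. That is the time over which natural change can accumulate.

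**Can the plan's 90 be reproduced?** No: the article names its sources but gives no effect size, SD or test. Back-solving the usual two-group formula (two-sided alpha assumed, since sidedness is not stated):

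d = (1.960 + 0.842) × √(2/45) = 2.802 × 0.2108 = 0.59

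This is a standardised difference between two arms of 45. It does not describe a one-arm change. For a paired test in 45 women, 80% power corresponds to a mean change of 0.43 SDs of the within-woman differences. That is a different quantity on a different scale, and it answers whether anything changed, not whether the intervention caused it.

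**How often could a within-IIG test be significant with no intervention effect?** Inputs: n = 45 (Sample size calculation) and alpha 0.05, taken as two-sided. Assumed, because the documents give neither: natural improvement δ in baseline SDs, and pre-post correlation r, with equal SDs at both times. With one arm and two time points, a repeated-measures analysis of a continuous score reduces to a paired t-test. For skewed counts this is an approximation.

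Standardised change: dz = δ / √(2(1 − r)). Noncentrality: dz × √45. Critical value: t with 44 degrees of freedom.

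For δ = 0.2:
- r = 0.3: dz = 0.2/1.183 = 0.169; noncentrality 1.13; probability of significance 0.199
- r = 0.5: dz = 0.2/1.000 = 0.200; noncentrality 1.34; probability 0.259
- r = 0.7: dz = 0.2/0.775 = 0.258; noncentrality 1.73; probability 0.395

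| Natural improvement (baseline SD) | r = 0.3 | r = 0.5 | r = 0.7 |
|---|---|---|---|
| 0 | 0.05 | 0.05 | 0.05 |
| 0.1 | 0.086 | 0.101 | 0.135 |
| 0.2 | 0.199 | 0.259 | 0.395 |
| 0.3 | 0.384 | 0.503 | 0.719 |
| 0.5 | 0.792 | 0.907 | 0.989 |

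If 30% of the 60 women in the IIG were lost, 42 would remain, and the row for 0.2 would read 0.188, 0.244 and 0.372. With a concurrent untreated arm showing the same natural change, the between-group rate would stay at 0.05.

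**The case against.** Both outcomes are openly labelled as change in the IIG. The article keeps the language of group differences for the randomised contrasts, and its Aims section ties efficacy to the comparison with a waitlist. A reader might infer that natural recovery will be reported as benefit. No passage says so, and the documents support only that it could be. This part of the objection stands.

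The sample-size sentence may be a condensed summary. Read literally it also covers acceptability, for which only a mean score across both groups is planned. The calculation also drew on a single-group pilot, so the pre-post outcomes may have been sized from pre-post data in the full protocol. This explains the wording but does not rescue it: as written, the sentence claims power for an effect that two of the listed outcomes cannot estimate.

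A reader might also infer that these outcomes are underpowered because only one arm contributes. The documents do not support that: 45 per group is stated, no assumed effect is given to set against it, and no shortfall can be shown.

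The missing comparator follows from a disclosed choice to offer every woman the intervention and to balance burden. One-arm follow-up is a natural consequence of that. The choice is not at fault; the status given to the resulting outcomes is. Nor does the Introduction say that every secondary outcome must be randomised, only that randomisation provides control for confounders such as time since the trauma. These two outcomes do not have that control.

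**Conclusion.** The point holds in a limited form. Two secondary outcomes are uncontrolled changes in one arm, and the article's power statement includes them among the outcomes on which the effect of the intervention is to be detected. This rests on the article's text alone and needs no assumption.

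The size of the risk does need assumptions. With no intervention effect, 45 women and a natural improvement of 0.2 baseline SD, a within-IIG test would be significant about 20% to 40% of the time for pre-post correlations of 0.3 to 0.7, against a nominal 5%. The rate rises with larger natural change and returns to 5% if there is none. No figure can be put on the share due to the baseline cut-off of two CB-IM, because the documents give no count distribution.

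The primary outcome and the 2-week CB-PTSS comparison are randomised contrasts and are unaffected. The matter limits what may be concluded at 6 weeks; it does not undermine the trial's main result.

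**What to change.** Three changes of wording, in the protocol and carried into the analysis plan:

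1. In Sample size calculation, limit the statement on effect and power to the between-group outcomes from baseline (T1) to 2 weeks after the immediate intervention (T3): number of CB-IM (primary) and CB-PTSS (secondary).
2. Present the IIG changes from baseline to follow-up as descriptive estimates of course, and the T3-to-T6 changes, already listed under Exploratory outcomes, as descriptive estimates of maintenance. Give each with a 95% confidence interval and the number of IIG women contributing (45 as planned).
3. State that efficacy conclusions rest only on the randomised T1-to-T3 contrasts, and add to the limitations that the 6-week results have no comparator.

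The cost is that two secondary outcomes lose their efficacy status. Data collection, visit schedule, randomisation and the primary analysis stay as they are.

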### Safety

Any serious adverse event occurring during data collection will be documented and reported to the competent ethics committee.

### Patient and public involvement

Participants will evaluate the intervention acceptability and will be able to give feedback on the intervention. Each participant will receive a personalised debriefing session. Study results will be sent to participants and shared with the public via social media and public events.

## Ethics and dissemination

Ethical approval of this protocol (dated 1 December 2022) was granted by the Human Research Ethics Committee of the Canton de Vaud (study number 2022-00652). The study sponsor is the Bureau du Promoteur de Recherche of the Lausanne University Hospital. Participants will provide an informed consent prior to study participation (see online supplemental material). The study will be monitored by an independent and certified data monitoring body. An initiation, intermediate and a closing visit will be realised on site by the independent study monitor. A scientific steering committee is consulted regularly for scientific decisions regarding the conduct of the study. This protocol was registered at ClinicalTrials.gov (NCT05381155) prior to data collection, in May 2022. Results of this study will be submitted for publication to peer-reviewed journals and presented in relevant conferences to ensure dissemination in the scientific community. Furthermore, data will be shared in an anonymised form, at the time of the publication of the related outcomes, in an open access register.

10.1136/bmjopen-2023-073874.supp1Supplementary data
